##### Carers

Carers allocated to the intervention group will receive a carer workbook.

ECHO will involve eight, weekly, individual online sessions, lasting 60 min, which will be delivered by assistant psychologists trained by the first and principal authors of the study (YM and [name]). During the sessions, the trained psychologist will encourage discussion about the information and exercises proposed in the workbook. In addition, for a deeper understanding of the contents of each session presented in the workbook, carers will read and do activities from the book “Skills based caring for a loved one with an eating disorder: The New Maudsley Method” (Treasure et al., 2011). (Spanish version: Los trastornos de la alimentación: guía práctica para cuidar de un ser querido Treasure et al., 2011). These sessions will also include some of the video-clips from the Digital Versatile Disc (DVD) for carers “How to Care for Someone with an Eating Disorder”^1^. This DVD includes practical strategies and techniques to help carers develop skills and knowledge to help their loved one move toward recovery and to look after their own wellbeing by following the “New Maudsley Approach.”

This book and the DVD are designed to help carers develop self-reflective skills in order to develop confidence, compassion and the courage to take risks. Both resources will show them how to experiment with changes in their caring behavior so they can be more helpful to a loved one suffering from an eating disorder.

The workbook and online sessions will provide a skills training programme that includes training in stress management, communication (based on motivational interviewing techniques), strategies to reduce accommodation and expressed emotion and to increase extinction training and new habits at home *via* effective social support.

### Outcomes

#### Patients

This study will consider primary and secondary outcomes measured at the four evaluation points: baseline (T0), post-intervention (T1), 3-month follow-up (T2) and 6-month follow-up (T3).

The following will be assessed as primary measures: ED symptomatology and psychological well-being. Secondary outcomes will include the following: body mass index (BMI), psychosocial adjustment, perfectionism, obsessive-compulsive symptomatology, motivation to change and hospital readmission. All outcomes and the instruments to be used are shown in Table 1.

**TABLE 1 T1:** Outcomes and measures/instruments.

	Outcome	Measure/instrument	References

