## Abstract

**Introduction:** One of the major problems with inpatient treatment of adolescent girls with an eating disorder (ED) is that the strategies learned during their hospital stay are not easily applied or maintained in their daily lives, and this has been related to high rates of relapse and readmission. The ECHOMANTRA programme was developed to optimize outcomes during and following inpatient or day-patient treatment. ECHOMANTRA is based on interventions for carers (Experienced Carers Helping Others, ECHO) and patients (Maudsley Model of Anorexia Nervosa Treatment for Adults, MANTRA) and is developed from the cognitive interpersonal model of anorexia (Schmidt and Treasure, 2006; Treasure and Schmidt, 2013). This study aims to describe the study protocol of a randomized controlled trial (RCT) for evaluating the efficacy of an adaptation of a novel intervention for patients and carers (ECHOMANTRA) to be implemented as an add-on to treatment-as-usual (TAU).

**Method:** In a multi−center pilot RCT, 80 female adolescent patients with a DSM-5 diagnosis of an ED and their carers will be invited to participate in the study. They will then be randomized to receive either the ECHOMANTRA intervention as an add-on to TAU or TAU alone. A repeated measures design will be conducted across four time points. Primary outcomes will be patient psychological well-being and eating disorder symptoms, and secondary outcomes will include body mass index, obsessive-compulsive symptoms, perfectionism, motivation to change and psychosocial adjustment. For carers, outcome variables will include psychological well-being, expressed emotion, accommodation and enabling behaviors, burden, and care skills.

**Discussion:** The results from this trial will establish the effectiveness of ECHOMANTRA and may reveal whether and to what extent this novel intervention can optimize outcomes during and following inpatient treatment. This study will also provide the adaptation of the ECHOMANTRA in the Spanish context for inpatient/day-care treatment.

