### Sample Size

An intention-to-treat method will be used to calculate sample size, considering the hypotheses for the primary outcome variables. Power calculations will be based on power determination for longitudinal designs with attrition (Hedeker et al., 1999), an alpha of 0.05, four assessment points (with baseline serving as a covariate), dropout rate of 40% and a fixed autoregressive coefficient of 0.40. A group size of 40 patients per group would provide 80% power with a bilateral *p* < 0.05 to detect a clinically significant change in eating pathology (overall Eating Disorder Examination Questionnaire, EDE-Q, of 0.45 points), assuming a standard deviation of one for the overall EDE-Q change scores (Hedeker et al., 1999), and also to detect a difference in mean weight gain of one Body Mass Index (BMI) point, which, based on previous research, would be clinically important to detect (Agras et al., 2000; Byrne et al., 2017). Therefore, if a sample loss of approximately 40% is taken into account, the participation of at least 70 participants per group will be required.

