**PATIENTS**			
1	Body mass index		
2	ED Symptomatology	Eating Disorder Examination (EDE-Q)	Fairburn and Beglin, 1994; Spanish Validation (SV): Peláez-Fernández et al., 2012
3	Eating pattern	Daily food self-reporting	
4	Psychological well-being	Depression Anxiety and Stress Scales (DASS-21)	Lovibond and Lovibond, 1995; SV: Bados et al., 2005
5	Psychosocial adjustment	Eating Disorders Quality of Life (EDQL)	Engel et al., 2006
6	Perfectionism	Child and Adolescent Perfectionism Scale (CAPS)	Flett et al., 1997^1^; SV: Castro et al., 2004
7	Obsessive-compulsive symptoms	Obsessive Compulsive Inventory-Revised (OCI-R)	Foa et al., 2002; SV: González et al., 2011
8	Adherence to treatment	Drop-out rate, number of sessions completed and task completion between sessions.	
9	Motivation to change	Visual analogue scale that assesses confidence and importance in changing symptoms of ED (*ad hoc*)	
10	Admission	Number of readmissions to hospital during the intervention and follow-up periods. Record medical history	
11	Patient feedback form	Patients’ satisfaction and experiences in the study.	

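### The sample size is said to cover the primary outcomes but is worked for EDE-Q and BMI (a secondary outcome), so the other primary, DASS-21, has no target difference, SD or power

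*Protocol article*

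**What the plan says.** **Primary outcomes.** The Outcomes section (Patients) states: "The following will be assessed as primary measures: ED symptomatology and psychological well-being". The Abstract agrees: "Primary outcomes will be patient psychological well-being and eating disorder symptoms, and secondary outcomes will include body mass index". Table 1 assigns EDE-Q to eating disorder symptoms and DASS-21 to psychological well-being.

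**BMI.** The same Outcomes section places it in the other group: "Secondary outcomes will include the following: body mass index (BMI), psychosocial adjustment, perfectionism".

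**Sample size.** The Sample Size section says the calculation was made "considering the hypotheses for the primary outcome variables". Its inputs are "an alpha of 0.05, four assessment points (with baseline serving as a covariate), dropout rate of 40% and a fixed autoregressive coefficient of 0.40". With 40 per group it claims 80% power at a two-sided 0.05 for an EDE-Q difference of 0.45 points (SD 1), "and also to detect a difference in mean weight gain of one Body Mass Index (BMI) point". It gives no SD for BMI and does not mention DASS-21. After allowing for about 40% loss it asks for at least 70 per group.

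**Analysis.** The Statistical Analysis section plans an ANCOVA with the pre-test score as covariate, then a repeated-measures analysis of variance. It does not say whether one or both primary outcomes must succeed.

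**The concern.** The pair of outcomes that is powered is not the pair that is named as primary. This is a contradiction in the printed text. It is not detail left to a fuller document, because the Sample Size section sets out its inputs and says which hypotheses it serves.

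Two things are at stake. First, a null DASS-21 result could not be interpreted against any planned sensitivity, although DASS-21 is one of the two outcomes on which the trial is to be judged. Second, the power claim uses the full 0.05 while two outcomes are primary. Whichever rule is later used to combine them, the paragraph has not allowed for its cost.

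**Working it through.** **1. Reproduce the EDE-Q figure.** Inputs from the Sample Size section: difference 0.45, SD 1, two-sided alpha 0.05, power 80%, autoregressive coefficient 0.40, four assessments with baseline as covariate.

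The variance factor for a constant arm difference over t equally spaced AR(1) measures is v = (1 + ρ) / [t − (t − 2)ρ].

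- Route A, three post-baseline measures: v = 1.4 / 2.6 = 0.538.
- n per group = 2v(1.960 + 0.842)² / 0.45² = 2 × 0.538 × 7.85 / 0.2025 = 41.7, so 42. Then 42 / 0.6 = 70, which is the document's final figure.
- Route B, four measures with linear attrition to 40% inside the formula (an assumed pattern): v = 0.515, which gives n = 39.9, so 40, the document's other figure.

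The EDE-Q arithmetic therefore reproduces at 40 to 42 per group, with power at 40 of 78% (A) or 80% (B). A single-visit two-sample comparison does not reproduce it: it needs 78 per group and has about 52% power at 40. The calculation thus appears to concern a difference taken over the repeated visits.

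**2. DASS-21 under the same model.** The difference detectable with 80% power at 40 per group, in SD units, is 2.802 × √(2v/40).

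- Route A: 2.802 × √(2 × 0.538/40) = 0.46.
- Route B: 2.802 × √(2 × 0.515/40) = 0.45.

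Power at 40 per group for assumed standardised differences, over both routes and with normal or t critical values:

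| Assumed difference (SD units) | Power |
|---|---|
| 0.2 | about 23% |
| 0.3 | 44–46% |
| 0.4 | 67–70% |

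The document does not say where in this range DASS-21 is expected to lie.

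**3. BMI.** For one point to be detectable with 80% power, the SD must be at most 1 / 0.46 = 2.2 (2.1–2.2 over the routes and critical values). For a single-visit comparison the limit is 1 / [2.802 × √(2/40)] = 1 / 0.626 = 1.6. The document gives no SD to set against either limit.

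**4. Two primaries at an unsplit 0.05.**

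- Either suffices: for independent tests the chance of at least one false claim is 1 − 0.95² = 9.75%. With bivariate normal test statistics it is 9.1% at correlation 0.5 and 8.3% at 0.7 (assumed correlations).
- Both required: alpha stays at or below 0.05. If DASS-21 has the same standardised effect of 0.45 and is independent of EDE-Q (assumed), joint power is 0.783² = 61% (A) to 0.801² = 64% (B).

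**The case against.** **Error control may be in the analysis plan.** Only the article is shown, and a rule for two primaries is commonly left to the statistical analysis plan. This stands: the absence of a rule is not a fault by itself. What the article does fix is a power claim at the full 0.05 and the wrong pair of outcomes, and a later plan cannot make that paragraph correct as written.

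**Much larger error rates.** A reader might infer that any one significant result would support efficacy, that three DASS-21 subscales are each tested, and that every visit is a separate test, so that the error rate runs far above 10%. The documents do not support this. No section says that one success suffices. Table 1 lists DASS-21 as one instrument for one outcome. The Statistical Analysis section plans a repeated-measures analysis, not a separate test at each visit. Only the 8–10% figure is defensible, and only if either outcome suffices.

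**The BMI claim as false.** A reader might infer this from a single-visit t-test. The section's own model is longitudinal. Under it an SD of 2.0 (standardised difference 0.5) gives about 85–88% power at 40 per group, so the claim may well be true. It is unsupported as written, not refuted.

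**Pilot status.** The Abstract and Study Design call the trial a pilot, and sizing on a single primary outcome is common. But Study Design also calls it a superiority study, and the Sample Size section claims 80% power for the primary hypotheses. Sizing on EDE-Q alone would be acceptable if the section said so.

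**Conclusion.** The point holds as a contradiction between the Sample Size section and the Outcomes section and Abstract. The EDE-Q calculation is sound on its own inputs. DASS-21, the other primary, has no planned sensitivity: the sample detects about 0.46 SD with 80% power, and power drops to 23% at 0.2 SD. The BMI statement belongs to a secondary outcome and depends on an SD that is not given.

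The cost of leaving the two primaries uncombined is moderate: an error rate of about 8–10% if either suffices, or joint power of about 61–64% if both are required. All DASS-21 and joint-power figures rest on assumed effects, the stated 0.40 autoregressive structure and 40 per group. They take 40 as the analysed number; the Abstract's 80 patients against at least 70 per group in the Sample Size section is a separate matter.

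**What to change.** **Testing order.** Name the arm difference in EDE-Q global score over T1–T3, the quantity the power calculation appears to use, as the first primary test at two-sided 0.05. Test the DASS-21 total second, in fixed sequence, only if the first test succeeds. This holds the overall error rate at 0.05, leaves EDE-Q power as calculated and needs no more patients.

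**Sample Size section.** Either relabel the BMI sentence as a power statement for a secondary outcome and give its SD, or delete it. Add the DASS-21 difference detectable with the planned sample (about 0.46 SD at 40 per group under the present assumptions), converted to DASS-21 points with a stated SD.

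**Cost.** Wording only. The small downside is that a success on DASS-21 alone becomes supportive rather than primary. The order is a choice for the sponsor to confirm; EDE-Q comes first here because it is the only primary outcome with a calculation.

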**PATIENTS**			
1	Body mass index		
2	ED Symptomatology	Eating Disorder Examination (EDE-Q)	Fairburn and Beglin, 1994; Spanish Validation (SV): Peláez-Fernández et al., 2012
3	Eating pattern	Daily food self-reporting	
4	Psychological well-being	Depression Anxiety and Stress Scales (DASS-21)	Lovibond and Lovibond, 1995; SV: Bados et al., 2005
5	Psychosocial adjustment	Eating Disorders Quality of Life (EDQL)	Engel et al., 2006
6	Perfectionism	Child and Adolescent Perfectionism Scale (CAPS)	Flett et al., 1997^1^; SV: Castro et al., 2004
7	Obsessive-compulsive symptoms	Obsessive Compulsive Inventory-Revised (OCI-R)	Foa et al., 2002; SV: González et al., 2011
8	Adherence to treatment	Drop-out rate, number of sessions completed and task completion between sessions.	
9	Motivation to change	Visual analogue scale that assesses confidence and importance in changing symptoms of ED (*ad hoc*)	
10	Admission	Number of readmissions to hospital during the intervention and follow-up periods. Record medical history	
11	Patient feedback form	Patients’ satisfaction and experiences in the study.	

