The ECHO part of the intervention focuses on carers. Based on the Model of Carer Coping (Treasure et al., 2003), this part of the programme reveals the different aspects that influence coping which can be problematic for carers as they represent sources of psychological distress. The programme provides assistance, support and training for carers to enable them to cope with their role. It teaches them how to reduce and manage their expressed emotion and symptom accommodation, and to deal with difficult and problematic situations that arise. In addition, ECHO teaches skills for positive communication and behavior change so carers will be able to support their loved ones in their recovery. Different studies using the ECHO have shown that the intervention in both the adult and adolescent groups led to a moderate reduction in time spent caring and also in bed use. Moreover, through this programme there was a small to moderate improvement in the wellbeing of both carers and patients in the intervention group (Hibbs et al., 2015a; Magill et al., 2016; Hodsoll et al., 2017). Our research group applied an intervention programme based on the ECHO to carers of ED patients in Spain. The results obtained showed that carers who participated in the programme improved their levels of well-being, reducing carer burden, psychological distress, and expressed emotion. In addition, only patients whose carers participated in the programme reduced their levels of anxiety, depression, and psychological distress while no change occurred in patients whose carers participated in the control group (Pérez-Pareja et al., 2014; Quiles Marcos et al., 2018). A recent review study analyzing the effectiveness of treatments for carers of ED patients concluded that ECHO also provides an intervention that can reduce service costs (Treasure et al., 2021).

The aim of this paper is to describe the study protocol of a randomized control trial (RCT) aimed at evaluating the efficacy of a novel intervention for patients and carers, called ECHOMANTRA, adapted to be used as an add-on to treatment-as-usual (TAU; inpatient treatment or intensive day-care treatment) compared to TAU alone.

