### Hypotheses

•Patients from the experimental group (TAU + ECHOMANTRA) will show significantly greater improvements in health outcomes (body mass index, ED symptoms, psychological well-being, psychosocial adjustment, perfectionism, obsessive-compulsive symptoms, motivation to change), and other efficacy indicators as readmission, in comparison to patients from the control group.•The efficacy of the combined intervention (TAU + ECHOMANTRA) will be stable in the short (6 months) and middle term (9 months).•Carers from the experimental group will present a better psychological well-being and lower illness accommodation, expressed emotion and burden in comparison to carers from the control group.•Carers from the experimental group will have more ED carer skills in comparison to carers from the control group.

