### Study Design and Procedure

This is a multi-center, pilot, randomized, controlled, blind, superiority study with two parallels groups. Assignment to the control or experimental group will carry out using a computer-generated randomized sequence, with1:1 treatment allocation. The research assistant at each center will conduct a semi-structured interview to evaluate participants and confirm fulfillment of the inclusion/exclusion criteria. Patients who are receiving ED treatment (either as inpatients or day-patients) and fulfill the inclusion criteria, will be invited to participate in the study together with a carer. By “carer” we refer to someone who usually takes care of the patient outside the hospital/day-center and lives with her. Patients and carers will receive detailed information on the study and will be asked for a written informed consent to be able to participate. After submitting the consent form, participants will be invited to complete the baseline questionnaires and will then be randomly assigned to either (1) ECHOMANTRA in addition to TAU or (2) TAU only (see Figure 1). The ECHOMANTRA-guided skills-sharing intervention will include materials and eight online sessions (one per week) for carers and patients, while treatment duration will be 8 weeks.

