### Interventions/Treatment Arms

#### Treatment as Usual

We have chosen not to use a standardized comparison treatment as this would require practical changes in different settings and resource management (including training, supervision and quality control), which will not be feasible. We have therefore chosen to allow centers to follow their own procedures for TAU. We will stratify our analyses by center, which will be adjusted accordingly for any bias.

For TAU inpatient care, the Eating Disorder Unit at the San Juan Hospital will provide a programme using a multidisciplinary team approach (dietician, psychologist, physician and nurse). It will include monitoring of physical risks, nutritional rehabilitation, education on healthy eating and nutrition patterns. Besides it will try to modify/improve thoughts, attitudes, behaviors and feelings that maintain the illness through psychological therapy. Once a patient has stabilized and reached a healthy body mass index, she is discharged. She is then either followed up to assess her progress and to facilitate transition to home or she is referred to a day care center.

Treatment-as-usual in the day care centers (ADANER and CREA) will involve multidisciplinary treatment including dietetic support, psychological interventions, school education, and when appropriate, sessions with psychiatrists. Patients will receive the following psychological interventions: weekly individual cognitive behavioral therapy for eating disorders (CBT-ED); and psychoeducational group therapy on nutrition, emotion management, body image, social skills and problem-solving strategies. Usually, patients attend every day of the week (from Monday to Friday) for an average of 6 h. They receive psychological intervention sessions and they also make the different meals of the day. Parents/carers can also access a fortnightly parent support group.

The TAU-only (control condition) group will have no access to the intervention materials or the ECHOMANTRA intervention sessions. At the end of the study, individuals randomized to the TAU-only condition will be offered the self-help components of the intervention.

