##### Clinical Assessment

The health care providers at the day care center or the 24-h hospital unit will submit the following information on the patient: BMI from monthly clinical measurement and up to 9 months post-randomization, diagnosis, age at onset of disorder, evolution of illness over time (duration), admissions prior to current one, comorbidity and readmission after being discharged.

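### The readmission outcome is a raw count that includes girls not at risk of readmission, so a never-discharged inpatient can only score zero and, read literally, a day-patient's first hospitalisation is missed

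*Protocol article*

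**What the plan says.** All references are to the protocol article.

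- **Table 1, Patients, row 10** (labelled Admission) gives the measure as "Number of readmissions to hospital during the intervention and follow-up periods", taken from the medical history.
- **Outcomes, Patients** ends its list of secondary outcomes with "motivation to change and hospital readmission". **Hypotheses** makes it a between-arm comparison: "other efficacy indicators as readmission, in comparison to patients from the control group".
- **Study Design and Procedure** invites "Patients who are receiving ED treatment (either as inpatients or day-patients) and fulfill the inclusion criteria". Randomisation follows consent and baseline, so counting opens while the girl is still in treatment. **Participants** names one inpatient unit and two day centres; the expected split of patients is not given.
- **Clinical Assessment** lists the items that care providers submit, among them "admissions prior to current one, comorbidity and readmission after being discharged". The list has no discharge date and no days in hospital for the current stay.
- **Treatment as Usual** says of the inpatient unit: "Once a patient has stabilized and reached a healthy body mass index, she is discharged". She is then followed up or referred to a day centre.

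**The concern.** A readmission requires a previous admission and a discharge from it. Row 10 opens its window at a point where neither is guaranteed. Inpatient entrants have not yet been discharged, and some day-centre entrants may never have been admitted to hospital. A zero can therefore mean that a girl recovered and stayed out, that she never left hospital, or that she was hospitalised for the first time. The first is the best course; the other two are poor ones.

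Time at risk also begins at discharge, which happens after randomisation and depends on clinical response, including BMI, which the intervention is hypothesised to improve. If the arms differ in discharge timing, a raw count compares unequal exposure. Relapse and readmission are the stated reason for the trial (Abstract, Introduction), so a result on this outcome will be read closely even though it is secondary.

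**Working it through.** The document gives no readmission rate, length of stay or power for this outcome, so there is no figure of its own to reproduce. The scoring follows from the text. The size of any bias needs assumed inputs.

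**1. Scoring under row 10, read with Clinical Assessment**

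| Course after randomisation | Score |
|---|---|
| Inpatient, discharged early, stays well | 0 |
| Inpatient, not discharged within the window | 0 (not at risk) |
| Inpatient, discharged, back in hospital once | 1 |
| Day-patient with an earlier admission, hospitalised again | 1 |
| Day-patient with no earlier admission, hospitalised for the first time | 0 (literal reading) |

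This step needs no assumption about the treatment effect.

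**2. Proportion readmitted, inpatient entrants, same hazard in both arms**

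Inputs: window W = 9 months (the span that Clinical Assessment states for BMI); hazard λ = 5% per month out of hospital (assumed); stay after randomisation L (assumed).

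P = 1 − exp(−λ(W − L))

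- L = 3: 1 − exp(−0.05 × 6) = 1 − exp(−0.300) = 25.9%
- L = 2: 1 − exp(−0.05 × 7) = 1 − exp(−0.350) = 29.5%
- L = 1.5: 1 − exp(−0.05 × 7.5) = 1 − exp(−0.375) = 31.3%

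With 3 months in control and 1.5 in the experimental arm, the spurious excess is 31.3 − 25.9 = 5.4 percentage points. The hazard ratio needed merely to show equality is (9 − 3)/(9 − 1.5) = 0.80; for 3 versus 2 months it is (9 − 3)/(9 − 2) = 0.86. Over hazards of 3% to 10% per month and stays of 3 v 1.5, 3 v 2 and 2 v 1 months, the excess is about 2 to 8 points. With equal stays it is zero.

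**3. Check with expected counts and variable stay**

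If time to discharge is exponential with mean m, mean time at risk is W − m(1 − exp(−W/m)) and the proportion never discharged is exp(−W/m). Taking W = 34 weeks (8 weeks of treatment plus 6 months), with equal true rates after discharge:

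| Mean stay, control v experimental (weeks) | Weeks at risk | Count ratio | Never discharged |
|---|---|---|---|
| 12 v 12 | 22.7 v 22.7 | 1.00 | 5.9% v 5.9% |
| 12 v 8 | 22.7 v 26.1 | 1.15 | 5.9% v 1.4% |
| 20 v 10 | 17.6 v 24.3 | 1.38 | 18.3% v 3.3% |

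With W = 39 weeks (9 months) the ratios are 1.00, 1.13 and 1.34. With fixed stays of 16 v 8 weeks and W = 34, the exposure ratio is (34 − 8)/(34 − 16) = 1.44, so a true rate ratio of 0.80 would appear as 0.80 × 1.44 = 1.16, on the wrong side of 1.

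**4. Dilution over the whole trial**

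Step 2 concerns inpatient entrants only. If one third of the 80 patients in the Abstract entered as inpatients (assumed), that is about 13 per arm. The excess is then 13 × 0.054 = 0.7 of a patient per arm, or 5.4/3 = 1.8 points trial-wide. If all 40 per arm were inpatients it is about 2 patients per arm.

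**The case against.** The strongest reply is that row 10 is a one-line table cell, that Clinical Assessment already supplies the natural qualifier, and that time at risk and the handling of undischarged patients are details an article leaves to a full protocol or analysis plan. Part of this stands: the absence of an exposure term from the Statistical Analysis section is not counted here. What is counted is the stated measure. Tying the event to discharge confirms that an undischarged girl cannot have it; it does not say how her zero is to be read.

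Several stronger readings are tempting, and the document does not support them.

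- *That the measure counts readmissions in girls still in hospital.* It cannot. The fault is that such girls enter the count without being at risk.
- *That day-patients were never in hospital.* Inpatients may be referred to day care and earlier admissions are recorded, so this holds for an unknown share only.
- *That the measure penalises the intervention.* It does so only if the index stay is shortened, which Hypotheses does not claim. The Introduction says that the carer programme "led to a moderate reduction in time spent caring and also in bed use", but fewer bed days can come from fewer readmissions as well as from earlier discharge. A 1.5-month stay would also end before the 8-week programme does.
- *That a rate could not be derived.* Row 10 draws on the medical history, from which dates may be retrievable, even though Clinical Assessment does not list them.
- *That the trial scores treatment failure as zero.* EDE-Q, DASS-21 and monthly BMI would still register a girl who does not improve.

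Mixing of settings is partly handled, since analyses are to be stratified by centre and centre separates the inpatient unit from the day centres. That does not change what a zero means within the inpatient unit or define the event for day-patients.

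**Conclusion.** The point holds as a defect in a stated outcome definition. Two parts are unconditional on any treatment effect: an inpatient not discharged within the window can only score zero, and on a literal reading a first hospitalisation of a previously unadmitted day-patient is not counted. How many patients the second part affects cannot be known from the document.

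The third part is conditional. If discharge comes earlier in the experimental arm, the count is biased against that arm among inpatient entrants, by about 2 to 8 percentage points under the assumed hazards and stays, and by fewer points over the whole trial. If discharge timing is equal, there is no bias. Every stay, every hazard and the inpatient share are assumptions. Readmission is secondary and plays no part in the sample size, so the stakes are moderate, but the change is worth making because readmission is central to the trial's rationale.

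**What to change.** 1. Reconcile Table 1 row 10 with Clinical Assessment. Define the event as any new hospital admission for the eating disorder after randomisation, first or repeat.
2. Report it separately for girls who entered as inpatients and as day-patients, with the number never discharged from the index admission in each arm.
3. Add to the Clinical Assessment list the index admission and discharge dates and the dates of each later admission and discharge.
4. Add, as a supporting measure, days in hospital (or readmissions per time since discharge) over one fixed window from randomisation, compared within or adjusted for entry setting. Fix the end of that window: the last assessment falls about 34 weeks after the start of treatment, while provider data on BMI run to 9 months.

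Days in hospital should not replace readmission outright. That would change the question, and because index days count, the total would depend heavily on who entered as an inpatient.

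The cost is a few more dates from a medical record that is already consulted, some protocol wording, and a skewed supporting outcome.
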